## Abstract

**Background:**

Chronic pain is associated with substantial personal suffering and societal costs and is a growing healthcare concern worldwide. While chronic pain has been extensively studied in adults, limited data exists on its prevalence and impact in adolescents. Understanding the prevalence and impact of chronic pain and pain beliefs in adolescents is crucial for developing effective prevention and treatment strategies. This study aims to estimate the prevalence, characteristics, and impact of chronic pain, and explore adolescents’ knowledge and beliefs about pain.

**Methods:**

This is an observational cohort study of school-going adolescents aged 11 to 17 years in Central Switzerland. The study will estimate the point prevalence, characteristics (location, intensity, frequency, duration) and impact (PROMIS Pediatric Short Form v2.0 –Pain Interference Scale, PPIS) of chronic pain in school-going adolescents. We will also measure and investigate pupils’ beliefs about pain (Concept of Pain Inventory (COPI)). Data will be collected through manual and digital self-report questionnaires and from participants in primary, secondary, and high schools between September 2023 and January 2024.

**Analyses:**

The primary analyses will utilise descriptive statistics to estimate the point prevalence, characteristics, and impact of chronic pain. Secondary analyses will analyse associations and correlations between chronic pain, impact of pain and beliefs about pain.

**Outcomes:**

This study will provide an estimate of the prevalence, characteristics and impact of chronic pain in adolescents in Central Switzerland and a measure of adolescents’ understanding and beliefs about pain. In doing so, this study will provide insights into the scale of chronic pain as a public health concern. By understanding adolescents’ pain beliefs and their influence on pain experience, this study can contribute to the development of educational approaches to enhance adolescents’ knowledge and understanding of pain in order to optimise the prevention and treatment of chronic pain in adolescents. The findings may be useful to healthcare professionals and funders, policymakers, and researchers involved in the prevention, assessment, and treatment of pain in adolescents.

## Introduction

Chronic pain is responsible for up to six billion Swiss Francs in direct and indirect costs in Switzerland each year [1] and is a growing problem worldwide [2–4]. In recognition of the prevalence and impact of chronic pain, chronic pain has been included in the new International Classification of Diseases (ICD-11) [4].

Chronic pain is a serious public health concern among adolescents, leading to diminished quality of life, absenteeism from school and greater use of medication [5–9]. Importantly, the early onset of chronic pain in youth increases the risk of chronic pain in adulthood [10]. Global estimates of the prevalence of chronic pain in adolescents from aged 11 to 17 years old vary from 3 to 37% [5,9,11,12]. This variability may be explained by different definitions of chronic pain, and data collection methods [9,12]. High quality prevalence studies have been recommended in order to provide more accurate estimates of the prevalence of chronic pain in adolescents [9,12,13]. In Switzerland, there is a lack of data on the prevalence of chronic pain in adolescents [14]. The latest estimate suggested a nationwide Swiss prevalence of 3% of chronic pain in adolescents [15]. However, this indirect estimate was based on the perception of paediatricians rather than a sample of Swiss adolescents directly [15]. Therefore, an estimate of the prevalence, characteristics and impact of chronic pain based on a sample of Swiss adolescents is urgently required.

In recent decades, it has become increasingly evident that knowledge and beliefs about pain can contribute to the duration of pain and pain-related disability in adults [16–19] and in adolescents [20,21]. Examples of common misconceptions about pain in adolescents are that pain always signifies harm, that the body needs rest and avoidance to heal, and that emotions do not influence pain [20,21]. These conceptions are connected to expectations, which in turn shape the experience of pain [22–26]. In addition to increased pain, expectations can also lead to avoidance behaviour [27–30]. These beliefs are at odds with contemporary understanding of pain science. While the majority of pain belief research has focused on adults, limited studies have identified the existence of some inaccurate and unhelpful beliefs in adolescents [28,31–33]. Further data is required to expand our understanding of conceptions of pain in adolescents [34].

Investigating the prevalence and impact of chronic pain and pain beliefs in adolescents will provide much-needed data and insights into the extent and nature of chronic pain in adolescents as a public health concern. Investigating adolescents’ knowledge and understanding of pain may help to develop educational strategies that contribute to the prevention and treatment of chronic pain in adolescents.

### Aims and objectives

The main aim of this project is to estimate the prevalence and impact of chronic pain in adolescents and to measure adolescents’ knowledge and beliefs of pain. The primary objectives are to:

Estimate the point prevalence of chronic pain among adolescents between 11 and 17 years of age in Central Switzerland.Investigate the characteristics (pain locations, duration, frequency, intensity) and impact of chronic pain in those adolescents experiencing it.

A secondary objective is to investigate adolescents’ knowledge and beliefs about pain; and to explore associations and correlations between chronic pain, the impact of pain, beliefs about pain, age and gender.

## Methods

This study has been registered on the Open Science Framework [35]. This study is being undertaken in part fulfilment of a Doctor of Philosophy (PhD) degree at University College Dublin (UCD) in partnership with Haute Ecole de Santé Vaud (HESAV, HES-SO). As a principal investigator (PI) (HS) leads the study, with guidance and support from an academic supervisor (KS) and co-supervisor (GC). The study is also supported by an international collaborator with subject expertise (JP) and an academic with statistical expertise (CB). The study is overseen by a Research Study Panel with an independent chairperson.

### Study design

This observational cohort study will employ a cross-sectional design. Data collection started in September 2023 and will last for approximately five months.

### Participants

Eligible participants include students aged 11 to 17 years attending classes in the second and third education cycle in Central Switzerland. The exclusion criteria for this study includes adolescents who decline to consent, and adolescents who cannot comprehend verbal instructions and/or read study documents in the German language.

### Setting

Participants will be recruited from primary, secondary and high schools in the cantons of Lucerne, Zug, Schwyz and Aargau, that is from the German speaking region in Central Switzerland. There is no evidence for different pain prevalence compared to other German-speaking cantons in Switzerland. All participating schools will be mixed/single gender, publicly funded and non-fee paying, and located in a mix of urban and rural areas of Central Switzerland. Study participants with an age range between 11 and 17 years will be recruited from participating schools. Currently, four schools with about 400 possible adolescents have provisionally confirmed their participation.

### Recruitment

The participating schools were contacted via mail to invite them to take part in the study. The objectives of the study and the data collection procedure were presented to the school principals to provide them with a comprehensive understanding of the study. The school principals have agreed to assist with recruiting participants. The study was promoted through mail advertisements within the participating schools. Once the teachers agreed to support the study, they received detailed information about the process. Schools and teachers have the option to withdraw their commitment to support the study at any time. In the event that a school decides to withdraw, possibly due to excessive effort required, other schools within the same region will be approached and invited to participate instead.

During official school class time, the teachers will verbally introduce the study to the pupils and provide them with the following documents:

Adolescents aged 11–13 will receive an adapted written information document, the written information document for the parent/ legal guardian and an invitation for the pupils and the parent/legal guardian to attend study information sessions (3 documents).Adolescents aged 14–17 receive another adapted written information document, the written information document for the parent/ legal guardian and an invitation for the pupils and the parent/guardian to attend study information sessions (3 documents).

The parents (or legal guardian) of the pupils will be introduced to the study via a study information letter and two optional online information events. School principals, teachers, parents/legal guardians and pupils will be able to contact the PI (HS) who will discuss the study and ask any questions via mail, telephone or an information session. The information session will take place online and in the evening on two different days within at least one week of participant enrolment. At the information event, scheduled to last approximately 45 minutes, the PI will present the aims and objectives of the project and what participation will involve.

Parents/legal guardians and pupils will be informed that study participation is entirely voluntary and that their children are free, without justification, to decline to participate or withdraw from the study at any time. Before data collection commences, the PI will explain the procedure in plain simple language to the adolescents again and screen them for eligibility to ensure that participants meet the inclusion criteria. The screening procedure will involve verbally asking the child if they can read and write in the German language. All pupils receive the same online link. As an additional verification of willingness to participate, adolescents can decide to complete the survey or a reading substitute task. If a participant chooses the reading substitute task, a text previously chosen by the teacher will appear on the screen instead of the survey.

### Ethics

For the majority of participants, this study carries no inherent risks. We acknowledge that completing questionnaires about chronic pain could cause emotional distress for some individuals. Should this occur, the primary investigator (HS) and the school teachers will liaise with participant and their parents/legal guardians to ensure that the healthcare needs are appropriately assessed. Furthermore, participants will be informed that they are free to withdraw from the study at any time and that there are no direct benefits to their participation. The study has been approved by the ethics committee for the northwest and central part of Switzerland (Ethikkommission Nordwest- und Zentralschweiz, EKNZ) (BASEC number: 2023–00891).

### Data collection

The PI (HS) will be present in the classroom together with the teacher to administer the link to the questionnaires or reading substitute task to all adolescents. This also ensures that direct enquiries can be made and compliance with the study protocol. Excluded children adolescents receive help from HS and the teacher to decide on the substitute task. Participating adolescents will be invited to complete questionnaires related to i) their demographics (age, gender, class grade), ii) the absence/presence of chronic pain, iii) pain characteristics and impact (those with chronic pain only), and iv) knowledge and beliefs about pain. The demographic data and the pain-related questionnaires will be completed via the cloud-based survey tool LimeSurvey. Piloting the questionnaires ensured that the questions were comprehensible and took approximately ten minutes to answer.

During the data collection period anonymised data will be stored digitally in the LimeSurvey cloud and will be accessible to the research team only. After each data collection session the data will be exported to and stored in a password protected folder on the Haute École de Santé Vaud in Switzerland for ten years. All data will be handled in accordance with current Swiss legislation [36]. On completion of the study we will make our anonymised data available without restriction on the Open Science Framework [35].

### Outcome measures

Sociodemographic data will be collected, including age (in whole years), gender (female, male, other, prefer not to say), and class grade (5^th^ to 6^th^ class primary school, 1^st^, 2^nd^ and 3^rd^ class upper school).

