#### Sample size

Previous studies have estimated that 3–38% of adolescents suffer from chronic pain. Assuming that 25% of our sample have chronic pain, this suggests that for a total of 288 responses, 95% confidence limits will be 20% and 30% with a precision of 5% (Sample size for prevalence surveys, © 2003–2005 Philippe Glaziou). With an estimated response rate of 80%, it is aimed to include 360 adolescents. The calculation is based on a population size of 86424 adolescents between 11 and 17 years in central part of Switzerland (canton Luzern, Aargau, Schwyz and Zug) in 2021.

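### The stated target is ages 11 to 17, but the listed class grades span only five school years; the two must be reconciled before an overall 11–17 prevalence is claimed

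*Protocol article*

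**What the plan says.** Four places in the Protocol article fix the target at ages 11 to 17:

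- Aims and objectives, first primary objective: "Estimate the point prevalence of chronic pain among adolescents between 11 and 17 years of age in Central Switzerland".
- Participants: "students aged 11 to 17 years attending classes in the second and third education cycle in Central Switzerland". Eligibility is thus bounded by school stage as well as by age.
- Setting: "Participants will be recruited from primary, secondary and high schools in the cantons of Lucerne, Zug, Schwyz and Aargau", again with an age range of 11 to 17. The Abstract names the same three school types.
- Sample size: "The calculation is based on a population size of 86424 adolescents between 11 and 17 years".

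Outcome measures is the only section that spells out classes. It lists "class grade (5^th^ to 6^th^ class primary school, 1^st^, 2^nd^ and 3^rd^ class upper school". No listed level is called high school, and the term upper school is not defined. The same sentence also collects "age (in whole years"), separately from grade.

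The Statistical analysis plan section promises one point prevalence with a 95% confidence interval and descriptive results by age and gender. It states no age quota and no age weighting. Limitations acknowledges non-random recruitment and selection bias but does not mention age coverage.

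**The concern.** Five consecutive classes cannot line up one-to-one with seven single-year ages. If the five listed classes are what is sampled, some target ages are thinly represented or missing, and the missing ages probably lie at the upper end. If later high-school classes are sampled too, the grade item as printed has no level for them. The text does not fit together under either reading.

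What is at stake is the population that the headline figure describes. One prevalence labelled 11–17 would be compared with other studies of that age range while resting mainly on a narrower span. Age is one of the factors whose association with chronic pain the protocol sets out to explore, so constant prevalence across ages cannot be presumed. A confidence interval for a single proportion reflects sampling error only. It would not widen or shift because part of the target population was not sampled.

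**Working it through.** **1. The plan's own figure.** Inputs from Sample size: "Assuming that 25% of our sample have chronic pain" and "for a total of 288 responses, 95% confidence limits will be 20% and 30% with a precision of 5" per cent; response rate 80%; population 86,424.

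n = 1.96² × 0.25 × 0.75 / 0.05² = 288.1. With finite population correction, 288.1 / (1 + 287.1/86,424) = 287.2. Both agree with the stated 288. Then 288 / 0.80 = 360, as stated. The half-width at n = 288 is 5.0 points.

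**2. Counting ages and classes.** Target ages 11, 12, 13, 14, 15, 16, 17: seven. Listed classes: two primary plus three upper school, five. Five classes have at most five modal ages, so at least 7 − 5 = 2 target ages are the modal age of no listed class. This needs no knowledge of which age sits in which class.

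**3. Expected share aged 16–17 if only the listed classes are sampled.** The article gives no ages per grade, so the following are assumptions: five classes of equal size; age at the start of 5th class 10, 11 or 12; 0–50% of pupils already one birthday older when surveyed; 0–20% one year over-age for their class. Shares are taken among respondents aged 11–17.

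| Assumed age at start of 5th class | Aged 16–17, of 288 | Share aged 16–17 | Share aged 17 |
|---|---|---|---|
| 10 | 0–6 | 0–2% | 0% |
| 11 | 0–40 | 0–14% | 0–2% |
| 12 | 58–94 | 20–33% | 0–12% |

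For comparison, seven equally sized year groups (also an assumption) give 2/7 = 28.6%, or about 82 of 288.

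The upper limit for a start at 11, with 50% one birthday older and 20% over-age, is built as follows:

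- Age 16 from the top class: (0.5 × 0.8 + 0.5 × 0.2)/5 = 0.10.
- Age 16 from the class below: (0.5 × 0.2)/5 = 0.02.
- Age 17 from the top class: (0.5 × 0.2)/5 = 0.02.
- Total 0.14, and 0.14 × 288 ≈ 40.

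With a start at 12 the upper ages are better covered, but 11-year-olds then fall below the first listed class.

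**4. Effect on the overall prevalence.** Let s be the share of respondents aged 16–17 and D the prevalence at 16–17 minus that at 11–15. The error in the overall estimate is (s − 2/7) × D. The values of D are assumed; the article gives none.

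| s | D = 5 points | D = 10 points | D = 15 points |
|---|---|---|---|
| 0 | −1.4 | −2.9 | −4.3 |
| 0.10 | −0.9 | −1.9 | −2.8 |
| 0.14 | −0.7 | −1.5 | −2.2 |

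The signs reverse if prevalence is lower at 16–17. The stated precision is 5 points.

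**5. What a small 16–17 group could support.** The half-width at 25% prevalence is 1.96 × √(0.1875/n): about 23 points with 14 respondents and about 16 points with 29.

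**6. Effect on sample size of narrowing the population.** Five sevenths of 86,424 is about 61,700. The corrected requirement becomes 288.1 / (1 + 287.1/61,700) = 286.8, so nothing changes in practice.

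**The case against.** The strongest reply is that the grade list describes a recorded variable and is not an eligibility rule. Eligibility runs to age 17, high schools are named as recruitment sites, and Recruitment provides a separate information document for ages 14 to 17. The list in a condensed article may be abbreviated, or upper school may include high-school classes. This stands as a reason for caution: the article does not prove that later classes are left out. It does not remove the inconsistency, because eligibility is also limited by education cycle and no other section says which classes are sampled.

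A reader might infer that 16- and 17-year-olds will be almost absent, appearing only through repetition or late entry. The documents do not support that. It needs an age for each grade that they do not give, and the result is sensitive to it: 0–6, 0–40 or 58–94 of 288 for a start at 10, 11 or 12. Even with a start at 11, ordinary birthdays bring some pupils in the last listed class to 16 during data collection from September to January.

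A reader might also infer that prevalence at 11–17 cannot be estimated. That goes too far as well. Age is recorded in whole years, so coverage can be seen and reported, and the estimate can be restricted to the ages observed or weighted by age where numbers allow.

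Finally, the prevalence differences used above are hypothetical, and the resulting errors lie within the stated 5-point precision. That is correct. They show what could go unnoticed, not that the estimate is biased.

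**Conclusion.** The point holds as an internal inconsistency that affects what the study may conclude. Seven target ages are set against five listed classes, and no quota or weighting is stated that would correct for the gap.

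If the listed classes are the frame and 5th class starts at about 10–11, ages 16–17 would make up about 0–14% of respondents instead of about 29%, and age 17 at most about 2%. The overall prevalence would then be off by up to about 1.4, 2.9 or 4.3 points for differences of 5, 10 or 15 points, the upper limit being reached when nobody is aged 16–17. These sizes rest on the assumed starting age, equal year sizes and assumed prevalence differences. The count of at least two uncovered modal ages needs only that the listed classes are the frame.

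The sample-size calculation reproduces and is not in question.

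**What to change.** Reconcile the class list in Outcome measures with Aims and objectives, Participants, Setting and Sample size in one of two ways:

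- **(a) Narrow the claim.** Restrict the stated target age range and the reference population to the ages covered by the classes actually sampled.
- **(b) Widen the coverage.** Add the later high-school levels to the grade item, include such classes from the high schools already named as a source, and make sure the education-cycle wording in Participants admits them.

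In either case, use the recorded age to report the achieved age distribution and age-specific prevalence with confidence intervals, and make no overall 11–17 claim if ages 16–17 are sparse.

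Option (a) costs only wording and a narrower claim, and it remains possible although data collection has begun. Option (b) costs some extra response options and a few more classes, and is open only while data are still being collected. Neither changes 288 or 360 in practice; replacing the 86,424 figure corrects the label of the population, not the sample size.

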#### Primary outcomes

The IASP defines chronic pain as “pain that persists or recurs for longer than 3 months” [37]. For the purpose of this study, we operationally defined the presence of chronic pain as the self-reported experience of recurrent or persistent pain for three or more months and a frequency of at least weekly [38–42]. This definition was chosen because it is the most commonly used and can therefore be compared with other studies from the field [9,12].

The presence/absence of chronic pain will be determined by participants’ self-reported responses to the following two questions:

“Chronic pain is defined as pain that is recurrent or persistent for 3 months or longer. Do you feel chronic pain?” Response options: “No, I don’t feel chronic pain”, “Yes, I have felt pain that has lasted 3 months or longer.”“How often do you feel this pain?” Response options: “daily”; “weekly”; “monthly”, or “rarely” [38,40,41].

Those adolescents with chronic pain according to the operational definition will be invited to provide self-report additional information in order to characterise their pain, including:

The location and total number of sites of their chronic pain, assessed via two body charts. The body chart is divided into 11 specific locations (head, neck, chest, shoulders, back, arms, hands, bottom/hips, belly/pelvis, legs, and feet) and an “other” category. For the first body chart, the child will be asked to mark the region in which they feel their most bothersome chronic pain. A second body chart will assess the number of chronic pain sites by the question: “Are there other areas where you have felt pain for 3 month or longer”. The chronic pain sites have a score range from 0 to 12 based on axis I of the IASP Classification of Chronic Pain [43] and has been used in previous studies investigating pain in adolescents [5,40,44]. Its reliability and validity are unknown.Usual pain intensity by asking, “How intense the pain feels usually?”, using an 11-point Numerical Rating Scale (NRS-11) (0 = no pain to 10 = the worst pain you can imagine”. This question provides a generic pain intensity and does not distinguish between pain at rest or activity [45]. The NRS-11 has been shown to provide reliable and valid scores when used with adolescents to assess current pain [46]. A high level of agreement in pain intensity ratings between the first and second measurements (Limits of Agreement: -0.9 to 1.2, 95% CI), indicating good reliability [46]. The NRS-11 has good convergent validity showing moderate to high correlations with other pain intensity scales [46]. Discriminant validity was supported by moderate correlations with measures of pain unpleasantness (r = 0.63) and functional impairment (r range: 0.35 to 0.43). The NRS-11 has demonstrated moderate correlations with measures of disability (r range: 0.22 to 0.39), psychological well-being (r range: 0.46 to 0.66), and pain interference (r = 0.62) [46]. Threshold values have been identified. Average scores of 3, 6, and 8 on the NRS-11 correspond to mild, moderate, and severe pain levels, respectively [46]. The NRS-11 has been used in a number of pain-related pediatric epidemiological studies [40–42].Pain duration by asking:” For how long have you felt this pain?”, with the response options: “3–6 months”, “6–12 months”, “1–2 years” or “over 2 years”. The validity and reliability of this retrospective question in adolescents is unknown. It has been used in numerous studies in adolescents [41,47–49] and will facilitate comparisons of results.The impact of their pain using the Patient Reported Outcome Measures Information System—Pediatric Pain Interference Scale (PROMIS-PPIS) short version in German [50]. PROMIS-PPI assesses self reported impairments in physical, psychological, and social functioning. The PROMIS-PPIS is an 8-item questionnaire studied in chronic pain children and adolescents, aged 2–17 years old. Scores range from 0 to 32 with higher scores indicating greater pain-related functional impairment. The PROMIS-PPIS is reliable [50] and has good internal consistency [51].
